#### Exclusion criteria

① Patients with liver metastases after local treatment such as ablation or transcatheter arterial chemoembolization;

② Patients with a history of allergy to egg or any type of ultrasound contrast agent;

③ Pregnant or lactating women;

④ Reluctant to perform contrast-enhanced ultrasound examination;

⑤ Severe heart disease, hypertension, severe liver and kidney dysfunction;

⑥ Pulmonary dysfunction;

⑦ Other conditions that are not suitable for ultrasound examination or enhanced CT/MRI examination.

### Schedule of the study

After obtaining informed consent, the study group will check both of the inclusion and exclusion criteria, participants' background and pregnancy status. Four training cases and 330 formal cases were included consecutively, and all subjects will be subjected to conventional ultrasound, Sonazoid-CEUS, CEMRI examinations, 65 of which should also be subjected to CECT examinations.

### Case screening period

According to the inclusion and exclusion criteria, patients are included continuously, and the basic information is collected after signing the informed consent form. Child-bearing age women need to have negative urine human chorionic gonadotropin for excluding pregnancy before inclusion.

### After inclusion

This study is divided into radiological examination (CECT/CEMRI) and ultrasound examination (conventional ultrasound and KPWLSM). Both parts are completed independently in a blind state of reading images and filling out the case report forms (CRFs). Either radiological or ultrasound examination start first is all right, and the interval between the two examinations is required from 24 h to 60 days.

### Ultrasound examination

#### Conventional ultrasound

All patients in the group will undergo conventional ultrasound first, and once any lesion is detected, the number, size, location according to Couinaud's classification and sonographic features will be recorded. The ultrasound examination will be performed on PHILIPS EPIQ Elite (Philips Healthcare, Bothell, WA) with a 6-1MHz convex transducer.

#### Sonazoid-CEUS

CEUS acoustic power was at the default setting with a mechanical index of 0.18 and a dynamic range fixed at 45–65 db. Sonazoid was reconstituted in 2 mL sterile water for injection. The injection dose was 0.01 mL of encapsulated gas per kg of body weight. Sonazoid was injected as a bolus at a rate of 1 mL/s, followed by a 5 mL normal saline flush.

a Vascular phase images were obtained 0–5 min after Sonazoid injection. For the lesions found from conventional ultrasound, the vascular-phase characters of them would be recorded, Kupffer phase (10–15 min) will be observed, and the relevant characteristics will also be recorded on the CRF.b If more than one nodule is found in pre-contrast conventional ultrasound, the largest one will be selected as target lesion, and more nodules should be observed at the same time if it is convenient in the same sonographic view. KPWLS were obtained at least 10 min after Sonazoid injection. If finding any additional defect in KPWLS, Sonazoid-CEUS would be repeated to observe the vascular character (for each patient, at most twice in one exam).c The whole process of ultrasound examination will be completed by two senior sonographers with at least 5 years of US experience and 3 years of CEUS experience. Two senior sonographers will assess the enhancement patterns according to WFUMB-EFSUMB guideline (14).

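### Sonazoid-CEUS is not masked to the conventional ultrasound scan that serves as its control, so a higher CEUS lesion count mixes contrast effect with an informed second look

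*Protocol article*

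**What the plan says.** All places are in the protocol article.

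- **Order.** Conventional ultrasound: "All patients in the group will undergo conventional ultrasound first, and once any lesion is detected, the number, size, location" and further features are recorded. The order is the same for everyone.
- **Operators.** Sonazoid-CEUS: "The whole process of ultrasound examination will be completed by two senior sonographers". No split of roles between the two scans is described.
- **CEUS builds on the first scan.** Sonazoid-CEUS: "For the lesions found from conventional ultrasound, the vascular-phase characters of them would be recorded", and "If more than one nodule is found in pre-contrast conventional ultrasound, the largest one will be selected as target lesion". For the Kupffer-phase sweep: "If finding any additional defect in KPWLS, Sonazoid-CEUS would be repeated to observe the vascular character".
- **Blinding.** After inclusion divides the study into a radiological part (CECT/CEMRI) and an ultrasound part (conventional ultrasound and KPWLSM), then states: "Both parts are completed independently in a blind state of reading images and filling out the case report forms (CRFs". Radiological examination blinds the two radiologists to other imaging. Image assessment withholds clinical information from readers.
- **Claim.** The comparison paragraph of the PICOT names conventional ultrasound as the control in a self-controlled, blind-read superiority trial. Primary endpoint treats a higher CEUS lesion count than both conventional ultrasound and CECT as success, and as confirmation of a diagnostic improvement due to Sonazoid-CEUS.
- **Test.** Data analysis plans a within-patient paired t-test on lesion numbers, two-sided at 0.05.

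**The concern.** The two tests being compared sit inside the same blinded part, so the blinding does not stand between them. The sonographers who run CEUS know what the conventional scan showed, are directed to those lesions, and then sweep the whole liver again. A lesion that appears only at the second sweep may have been revealed by contrast, or it may have been found because the liver was examined twice by people who knew what had already been seen. The design cannot tell these apart: there is no masked reading, no variation of order and no second unenhanced look.

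At stake is the interpretation of one arm of the primary comparison. A positive result against conventional ultrasound would be reported as a contrast effect shown under blind reading, and neither part of that description would be secured.

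**Working it through.** **1. Does any stated safeguard cover CEUS against conventional ultrasound?**

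| Section | What is kept apart | Covers CEUS vs conventional? |
|---|---|---|
| After inclusion | Radiology part from ultrasound part | No, both are in the ultrasound part |
| Radiological examination | Radiologists from other imaging | No |
| Image assessment | Readers from clinical information | No, the conventional scan is not named |

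**2. How sensitive is the planned test to a few extra lesions?**

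Inputs: 330 patients and 10% dropout (Sample size), so n = 330 × 0.90 = 297; paired t-test, two-sided 0.05 (Data analysis).

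Let g patients gain one lesion on CEUS, l patients lose one, and the rest be equal.

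- mean difference = (g − l)/n
- s² = [(g + l) − (g − l)²/n]/(n − 1)
- t = mean/(s/√n), with n − 1 degrees of freedom

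| Gains | Losses | Mean | SE | t | p |
|---|---|---|---|---|---|
| 4 | 0 | 4/297 = 0.0135 | 0.0067 | 2.01 | 0.045 |
| 9 | 0 | 9/297 = 0.0303 | 0.0100 | 3.04 | about 0.003 |
| 4 | 1 | 3/297 = 0.0101 | 0.0075 | 1.34 | 0.18 |
| 9 | 3 | 6/297 = 0.0202 | 0.0116 | 1.74 | 0.083 |

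Four patients are 4/297 = 1.3%. That threshold applies only when nobody loses a lesion; one loss removes significance.

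**3. What could a second look do with no contrast effect at all?**

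This was simulated with 297 patients and 1,500 runs per setting. Sensitivity of conventional ultrasound and prevalence come from Sample size (62.5–87.7% and 25–50%; 75% is an intermediate value). Three things are assumptions that are not in the documents: every first-scan lesion is carried into the CEUS count, the second look recovers 10% of missed lesions, and affected patients have on average 1, 2 or 3 metastases. The table shows the share of trials that declare CEUS superior.

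| First-look sensitivity | Prevalence | 1 lesion | 2 lesions | 3 lesions |
|---|---|---|---|---|
| 62.5% | 25% | 29% | 77% | 95% |
| 75% | 50% | 49% | 92% | 99% |
| 87.7% | 25% | 1% | 11% | 25% |

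With an independent second reading of equal sensitivity, the share is 2–3%, against a nominal 2.5% in that direction. Varying the recovery from 5% to 20% widens the carry-forward range to between 0.1% and 100%.

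**4. How does this compare with the planned gain?**

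The second-look recovery that would by itself produce the assumed rise in sensitivity is (new − old)/(1 − old).

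- 62.5% to 73%: 0.105/0.375 = 28% of missed lesions
- 87.7% to 95%: 0.073/0.123 = 59% of missed lesions

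At the lower end of the planning range a moderate second-look yield could account for the whole planned difference; at the upper end it would have to be large.

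**The case against.** A reader might infer that the CEUS count equals the conventional count plus whatever is added, so that CEUS cannot lose and 1.3% of patients with an extra lesion guarantee superiority. The documents do not support that.

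- The article writes no such counting rule. The reference to additional defects triggers a repeat examination; it does not define the endpoint. A lesion without a Kupffer defect, or one reclassified, can leave the CEUS count.
- Sample size assumes specificity of 40–60% for conventional ultrasound and 65–75% for CEUS. If counts are lesions called metastatic by each modality, CEUS is expected to drop some conventional findings. If counts are reference-confirmed metastases, the assumed sensitivity ranges (62.5–87.7% and 73–95%) overlap, so losses are not excluded.
- No second-look yield appears in the documents, and the simulated rates in step 3 depend on assumed carry-forward.
- Beating conventional ultrasound is not enough for success. Primary endpoint also requires more lesions than CECT, which separate radiologists read blinded.
- Scanning without contrast first is natural when Sonazoid imaging can last more than an hour (Introduction), and CEUS as an add-on is a legitimate question.

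All of this stands, and it limits the size of the point. It does not restore masking. A condensed article may leave reader logistics to the full protocol, but this one does set out the ultrasound workflow, and in that workflow CEUS is guided by its own control.

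**Conclusion.** The point holds in a limited form. Fixed order, shared operators and CEUS directed by the conventional findings are all written in the article, and none of its blinding statements masks CEUS to conventional ultrasound. The comparison therefore combines contrast with an informed second look and leans towards CEUS. Primary endpoint cannot attribute a higher CEUS count to Sonazoid alone or treat it as blind-read superiority over conventional ultrasound.

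The size of the bias is unknown. The p=0.045 from four gains shows how little is needed if losses are absent, and the p=0.18 after one loss shows how much rests on that condition. The comparison with CECT is untouched.

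**What to change.** 1. Lock the conventional-ultrasound case report form before Sonazoid is injected.
2. Record the KPWLS lesion list separately. Do not carry conventional lesions forward automatically; a reference-confirmed metastasis on the conventional form that KPWLS does not show counts as a CEUS miss. Match lesions only after both lists are locked.
3. In the comparison paragraph of the PICOT and in Primary endpoint, restate the conventional-ultrasound comparison as the incremental yield of adding Sonazoid-CEUS to conventional ultrasound.
4. Keep the superiority wording only if the KPWLS sweep is done by a sonographer masked to the conventional result, with the two existing sonographers alternating roles across patients. A fixed allocation of one sonographer per modality would confound operator with modality.

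**Cost.** Items 1 to 3 need form handling and wording, with no extra examinations, and lead to a less favourable claim. Item 4 needs no extra staff, but the masked sonographer must stay out of the vascular-phase imaging until the sweep, which starts at least 10 minutes after injection. The session becomes less convenient, and each ultrasound modality has one reader at first read instead of a two-reader consensus.

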#### Radiological examination

Patients may have CECT/CEMRI tests before or after ultrasound, and the interval should be between 24 h and 60 days. After completion of the examination, the images will immediately acquire blind desensitization treatment to ensure blinded reading. Then two senior radiologists will evaluate the images blinded to the other imaging.

#### CT

Liver CT will be performed on 320-detector scanners. Precontrast CT images will be obtained first, and then image acquisition in the arterial, portal venous, and delayed phases will begin 40, 70, and 180 s after intravenous administration of an iodinated contrast agent (iopamidol; Iopamiron 350, Nihon Schering, Osaka, Japan) at a dose of 100 mL and an infusion rate of 3 mL/s (15).

#### MRI

Liver MRI will be performed on 1.5 T or 3.0 T MRI scanners using a contrast agent (Gd -DTPA, Magnevist®, Bayer Health Care Pharmaceuticals, Berlin, Germany). All patients will accept standard MRI sequences, and the injection dose was 0.1 mmol Gd/kg body weight. Image acquisition in the arterial, portal venous phases, and late-dynamic phases will begin 10, 45, 120 and 180 s after intravenous administration of contrast agent at an infusion rate of 2 mL/s followed by a 30 mL saline flush.

#### Image assessment

Images of the lesions are to be saved as image files and the lesions should be marked with arrows. The readers will be asked to evaluate the whole liver images and pick up all lesions without any clinical information. When the consensus is reached after discussion, they will fill in the CRFs. The study coordinators will examine the correlation between these image files with their pathological and multi-imaging findings including follow-up imaging, and also collect all images and CRFs for specialized storage in the database.

#### Reference diagnosis

For patients undergoing hepatic surgery or biopsy, the final diagnosis for the target liver lesion in each patient will be determined based on the pathological results.

Not all cases have histological results, so a comprehensive clinical assessment including CEMRI, clinical or laboratory indicators is needed to determine whether the lesions are metastases. And the duration of follow-up for the controversial lesions is assigned as 1 year.

#### Primary endpoint

The primary study endpoint is the comparative analysis of the number of detected liver metastatic lesions among Sonazoid-CEUS, conventional ultrasound and CECT in screening liver metastases. If the results show that Sonazoid-CEUS could detect more lesion than conventional ultrasound and CECT, the study will be considered to be successful because it means the data collected in the present study confirmed the diagnostic improvement provided by Sonazoid-CEUS over conventional ultrasound and CECT, Sonazoid-CEUS will be confirmed as an excellent screening tool without radiation exposure.

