#### Secondary endpoint

The secondary endpoint is the comparative analysis of diagnostic accuracy between Sonazoid-CEUS and CECT in a single lesion. When the results show that Sonazoid-CEUS provide better diagnostic efficacy than CECT, the study will be considered to be successful because it means the data collected in the present Sonazoid-CEUS could be a potential diagnostic tool instead of CECT despite the good diagnostic performances achieved by the latter.

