#### Sample size

As sample size calculation is closely related to research design, and this study consists of several parts which involves the comparison of superiority and diagnostic accuracy, so the calculation of multiple sample sizes is carried out, followed by the larger size as the final calculation results.

For the comparison of superiority and diagnostic accuracy between conventional ultrasound and Sonazoid-CEUS, we assumed a 25–50% prevalence of liver metastatic lesions in our target population (17), while 62.5–87.7% of sensitivity, 40–60% of specificity in conventional ultrasound (12), and 73–95% of sensitivity, 65–75% of specificity in Sonazoid-CEUS according to previous literature studies (18, 19). Also, a 10% dropout rate is included, and the required number of subjects is calculated to be 330.

For the comparison of superiority and diagnostic accuracy between CECT and Sonazoid-CEUS, we also assumed a 25–50% prevalence of liver metastatic lesions in our target population, while 90% of sensitivity in CECT (19), and 73–95% of in Sonazoid-CEUS according to previous literature studies. Since no AUC has been reported, this study attempted to use AUC of 0.75, 0.85, 0.95 for sample size calculation, and a 10% dropout rate is included. The required number of subjects for this part is calculated to be 65.

The sample size was calculated on the non-parametric module of PASS software using paired non-parametric test. With all these assumptions, a minimum of 330 patients are needed to obtain 80% or 90% statistical power for non-parametric test with an α equal to 0.05, of which at least 65 cases need to have received CECT.

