### Data analysis

A commercially available software package (SAS version 9.2, SAS Analytics, Marlow, UK) will be used for all the statistical analysis, and the significance level was 0.05 for two-sided tests. Descriptive data will be mainly used in the study. Efficacy analyses of sensitivity, specificity, positive predictive value, negative predictive value and accuracy will be performed using the efficacy population including subjects who received Sonazoid-CEUS, conventional ultrasound, CECT and CEMRI in screening liver metastases.

For the comparison of superiority among Sonazoid-CEUS, conventional ultrasound and CECT, intra-individual comparison will be made in terms of the detection rate of the number of detected liver metastatic lesions with pared-samples *T*-test. And the Chi-square test or Fisher exact test will be used to compare the diagnostic accuracy of the three imaging modalities in screening liver metastases.

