In 2016, a comparative study between CECT and Sonazoid-enhanced ultrasonography diagnosis of hepatic metastases in 148 nodules found that there was no statistical diagnostic difference between the two, and CEUS detected 19 occult lesions unrecognized by the use of CECT and 12 lesions were confirmed malignant by histopathology (12). Although several similar studies have investigated the diagnostic accuracy of CEUS in hepatic metastases, most of them are based on retrospective analyses of clinical data and radiologic findings (9, 24). Therefore, the present study would further verify the application value of Sonazoid-enhanced ultrasonography in screening liver metastasis prospectively. If the results show Sonazoid-CEUS provide better diagnostic performance than conventional ultrasound and CECT through diagnostic efficacy comparison, that would mean Sonazoid-enhanced ultrasonography has potential benefit in screening liver metastasis without having to refer cancer patients for additional CT or MRI.

Besides, as Sonazoid became clinically available in April 2019 in China after Japan, South Korea and other countries, several related domestic studies have been reported about the application value of Sonazoid for focal liver lesion especially in hepatocellular carcinoma, but few studies focused on metastatic liver tumors (25–27). A small-sample study with 27 patients (99 metastatic liver lesions) found contrast-enhanced intraoperative ultrasonography of Sonazoid may play a similar or even better role than other radiological methods (intraoperative ultrasonography and MRI) in diagnosing liver metastasis, and 8 occult metastatic lesions were newly found in 7 of the 27 patients, thus to change relevant treatment strategy (28).

With larger patient population, the current study will provide fundamental data of the size and location of metastatic lesions to explore the indications, application range of Sonazoid-CEUS in screening liver metastasis. We will also analyze how influential factors such as position, echogenity and other unknown factors eliminate the use of Sonazoid CEUS and explore how to improve it.

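### A higher lesion count alone confirms Sonazoid-CEUS as a screening tool, with no role for false positives, and the secondary endpoint is a second, unordered route to study success

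*Protocol article*

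**What the plan says.** The Primary endpoint section of the Protocol article compares the number of liver metastatic lesions found by Sonazoid-CEUS, conventional ultrasound and CECT. It then gives a decision rule: "If the results show that Sonazoid-CEUS could detect more lesion than conventional ultrasound and CECT, the study will be considered to be successful". It infers an improvement in diagnosis, and that "Sonazoid-CEUS will be confirmed as an excellent screening tool without radiation exposure".

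The Secondary endpoint section, on diagnostic accuracy against CECT in a single lesion, has its own rule: "When the results show that Sonazoid-CEUS provide better diagnostic efficacy than CECT, the study will be considered to be successful". The conclusion attached there is that CEUS might replace CECT as a diagnostic tool. Neither section makes its rule depend on the other.

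Four other sections bear on this:

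- **Image assessment:** "The readers will be asked to evaluate the whole liver images and pick up all lesions without any clinical information".
- **Reference diagnosis:** pathology where available; otherwise "a comprehensive clinical assessment including CEMRI, clinical or laboratory indicators is needed to determine whether the lesions are metastases".
- **Data analysis:** for superiority, "intra-individual comparison will be made in terms of the detection rate of the number of detected liver metastatic lesions", by a paired t-test. Sensitivity, specificity, predictive values and accuracy are also planned, with a test comparing accuracy across the three modalities. One two-sided level of 0.05 is given. None of these measures is tied to the primary success rule.
- **Sample size:** "73–95% of sensitivity, 65–75% of specificity in Sonazoid-CEUS"; 62.5–87.7% and 40–60% for conventional ultrasound; 90% sensitivity for CECT with no specificity; prevalence 25–50%.

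**The concern.** A test can find more lesions simply by calling more things lesions. A rule that looks only at the number found cannot tell better detection from a lower threshold, so it cannot by itself support a claim about screening. The Discussion describes the hoped-for benefit as screening "without having to refer cancer patients for additional CT or MRI". False alarms generate exactly those examinations, so they bear directly on the claim.

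The second success statement is a separate fault. As written, a trial that misses its primary endpoint can still be reported as successful on the secondary one, with no ordering of the tests and no adjustment of the significance level.

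**Working it through.** **1. The plan's own figures.** The plan gives no false-positive count and no error rate for declaring success, so there is nothing of that kind to reproduce. The sample sizes of 330 and 65 are taken as stated. They cannot be uniquely reproduced because the inputs are ranges and power is given as 80% or 90%, but nothing below depends on reproducing them.

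**2. What the count depends on.** Let p be prevalence, Se sensitivity and Sp specificity. Per candidate:

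- confirmed metastases detected = p × Se
- all lesions marked = p × Se + (1 − p)(1 − Sp)
- accuracy = p × Se + (1 − p) × Sp

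The first contains no Sp. The second rises as Sp falls. To show that nothing restrains the rule, take p = 0.25, conventional ultrasound at the top of its stated ranges, and CEUS with a deliberately poor specificity of 0.20. That value is hypothetical and far below the plan's 65–75%.

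| | Se | Sp | confirmed | all marked | accuracy |
|---|---|---|---|---|---|
| Conventional ultrasound | 0.877 | 0.60 | 0.219 | 0.519 | 0.669 |
| CEUS | 0.95 | 0.20 | 0.2375 | 0.8375 | 0.3875 |

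CEUS wins on either count, although its accuracy is 28 points lower.

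**3. CECT, within the plan's stated sensitivities.** Take Se = 0.95 for CEUS and 0.90 for CECT. At p = 0.25 CEUS detects more: 0.2375 versus 0.25 × 0.90 = 0.225. Its accuracy is nevertheless lower whenever CECT specificity exceeds CEUS specificity by more than p × (0.95 − 0.90)/(1 − p):

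- p = 0.25: 0.0125/0.75 = 1.7 points
- p = 0.50: 0.025/0.50 = 5 points

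With CEUS at 75%, a CECT specificity above 76.7% or 80% respectively would suffice. The plan states no CECT specificity, so which side of that line the trial lies on is unknown.

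**4. False positives at the planned specificities.** Read the prevalence as patient-level (an assumption). Patients without metastasis number 330 × 0.50 = 165 to 330 × 0.75 = 247.5.

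- CEUS: 165 × 0.25 = 41 to 247.5 × 0.35 = 87
- Conventional ultrasound: 165 × 0.40 = 66 to 247.5 × 0.60 = 149
- CEUS within the 65 CECT patients: 32.5 × 0.25 = 8 to 48.75 × 0.35 = 17

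CEUS positive predictive value runs from 0.1825/(0.1825 + 0.2625) = 41% to 0.475/(0.475 + 0.125) = 79%.

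**5. Two routes to success.** Assume that each rule requires significance at two-sided 0.05, that is, 2.5% in the favourable direction. If the routes were independent, the chance of at least one false success is 1 − 0.975² = 4.9%. Under any dependence it cannot exceed 2.5% + 2.5% = 5%.

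**6. Precision against CECT.** With 33–49 patients free of metastasis among the 65, and an assumed 20–30% of paired readings discordant, the 95% half-width for the specificity difference (taken near zero) runs from 1.96 × √(0.20/49) = 13 points to 1.96 × √(0.30/33) = 19 points.

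**The case against.** The endpoint is named as metastatic lesions throughout, and there is a reference diagnosis to decide which lesions those are. Read that way, a false positive is not a detection. This largely answers the worry that false alarms are counted as wins, although the success sentence itself drops the word metastatic. It does not answer the other half: a count of true metastases measures sensitivity only.

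Specificity and predictive values will be analysed, so a poor false-positive rate would be visible. The Discussion also ties the saving of CT or MRI to better diagnostic performance. Both points stand, but neither changes the rule in the Primary endpoint section.

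Three stronger readings are tempting, and the documents do not support them:

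- *Either route endorses CEUS for screening whatever its false-positive rate.* The secondary route uses diagnostic accuracy, which false positives reduce, and concludes only that CEUS may be a diagnostic tool. The false-positive gap belongs to the primary route.
- *The plan's figures predict excess false alarms.* Against conventional ultrasound they predict fewer (41–87 versus 66–149). Against CECT no excess can be shown, because no CECT specificity is given.
- *The false-success rate doubles.* About 5% is a ceiling. The primary must beat both comparators, and both routes compare CEUS with CECT in overlapping patients, so positive correlation is likely and would lower the figure.

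Ordering of endpoints is often left to an analysis plan. Here, however, the article does not leave the matter open: it states an unconditional second success.

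**Conclusion.** The point holds in two parts. First, the primary rule draws a conclusion about screening from a quantity in which specificity plays no part (confirmed metastases) or in which poor specificity is an advantage (all marked lesions). The exposure is chiefly against CECT, where a specificity deficit of as little as 1.7 to 5 points could offset the best-case sensitivity gain in overall accuracy. That range rests on sensitivities of 95% and 90% and a prevalence of 25–50%. Whether such a deficit exists cannot be told from the documents.

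Second, the secondary endpoint can make the study successful after a failed primary. This raises the chance of a false success in the favourable direction to at most about 5% instead of 2.5%, assuming each rule means significance at two-sided 0.05. The structural fault does not depend on the exact figure.

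The data remain usable. It is the declared conclusion that would not follow, so the wording should be corrected before analysis.

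**What to change.** (a) In the Primary endpoint section, state that the lesions counted are reference-confirmed metastases, and limit the success claim to improved detection. Draw the screening-tool conclusion only together with the paired difference in specificity, or in false-positive lesions per patient, against each comparator with its 95% confidence interval. A formal non-inferiority margin against CECT should not be required: with 65 CECT patients the interval would span roughly 13 to 19 points either side, and a tight margin would need more CECT patients.

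(b) In the Secondary endpoint section, delete the statement that the study will be successful. Test that endpoint only after primary success, in fixed sequence, and call it supportive. This keeps the false-success chance at no more than 2.5% in the favourable direction.

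The cost is mainly wording. Readers already mark every lesion and a reference diagnosis is already planned, so no new examination is needed. The downside is that success becomes somewhat harder to declare, and the specificity comparison with CECT will be imprecise.
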